### 7.3.3 Quality of Decision Making

The responses to each question (including the amount of missing responses) and the calculated total scores of the decisional questionnaire will be summarised descriptively overall and broken down by host trial, TRECA allocation and type of questionnaire (younger patient, adolescent or parent/family). A bar chart showing the total scores for each of the three TRECA arms will be included.

As a patient and their parent/carer may both fill in a questionnaire, all the data from the all three questionnaires will not be combined, as all the scores would not be independent. Hence, scores for patients (younger or older) and parents/family questionnaires will be analysed separately using a linear regression, with TRECA allocation and host trial status (whether the participant went on to enter the trial) included as a covariates. Clustering will be accounted for by using the cluster variable as a random effect. Mean difference will be presented with 95% confidence intervals.

If both the younger and older patient questionnaires are used in a host trial the questionnaire data from the younger and older patient questionnaires will be combined. The scores for these will be standardised within the trial by subtracting the sample mean score from the observed score and dividing the result by the sample standard deviation, where the ‘sample’ refers to the subset of participants that have used that questionnaire. Then the standard scores for all participants will be analysed as described above.

To assess the robustness of the method used to replace the missing values, a sensitivity analysis will be conducted, where the analysis will be repeated using only the questionnaires in which all 9 questions were answered.

Both the above analyses (in this section) will be repeated for only the participants who went onto to enter a trial.

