# Trial Objectives

The immediate aims of TRECA are to evaluate the potential for MMIs to improve the quality of decision making about participation in healthcare trials involving children and adolescents, and to assess the impact on trial recruitment and retention.

The long-term aim of the project is to increase the available clinical evidence base for the treatment of children and adolescents, including those with long-term health conditions.

The aim of this phase of TRECA is to evaluate the MMI in a series of SWATs, and test their effects on recruitment and retention rates, and decision-making, by comparing the effects of providing standard written participant information with provision of the MMIs either in addition to the standard written participant information or the provision of the MMIs alone.

Hence, the two pairwise comparisons of the three TRECA arms of interest are whether the MMI provision could replace (MMI only vs PIS only) or supplement (MMI & PIS vs PIS only) the standard written participant information. The results of the individual trials will be combined statistically in a meta-analysis, as described in Section 8.

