# Sample Size

## 4.1 Overall

The sample size for each SWAT will ultimately be determined, and constrained, by the number of people approached to take part in the host trial.

An example sample size calculation based on the expected baseline recruitment rate of the host trials (that is, their recruitment rate without the intervention), is provided. A baseline recruitment rate of 20% to 80% is assumed, to account for the known variation in trial recruitment rates. Given this uncertainty, we estimated the sample size based on the relative effect of the MMI alone (when compared to PIS alone). Further, we assumed 80% power at standard 5% Type I error (α rate) to detect the specified effect and we have characterised the effect size as an odds ratio, which is more robust for sample size calculation.

Assuming the typical recruitment rate is 20%, an odds ratio of 1.2 would mean an increase in recruitment rate using the MMI to 23.1%. To detect this in a single randomised controlled trial (with 1:1 randomisation between MMI and printed material arms), a sample size of 701 would be needed. If the typical recruitment rate is 80%, an odds ratio of 1.2 corresponds to an increase in recruitment rate to 82.8% and would require a sample size of 783.

Results from each embedded trial will ultimately be combined in a meta-analysis. Given that there will be different trials with variation in interventions, participants and baseline recruitment rates, it is plausible that the effectiveness of the MMIs at improving recruitment will vary; i.e. there will be heterogeneity in the observed odds ratios across trials. Adjusting for this is approximate (particularly as the heterogeneity is currently unknown), however, as a rough rule of thumb if the I2 statistic in the meta-analysis is 50% the sample size will double (1).

Given the three arm randomisation (with two of the arms being compared for the primary analysis), an additional 50% of people will need to be approached (i.e. 783 x 1.5 = 1,175). Furthermore, the adjustment for heterogeneity in effects of the MMI intervention across the six trials (estimated I-square value = 50%) means that the sample size should be doubled (i.e. 1,175 x 2 = 2,350).

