# Outcomes

## 6.1 Primary outcome (Recruitment - MMI only vs PIS only)

The primary outcome is recruitment to each host trial between the MMI only arm and the PIS only arm. For recruitment we will calculate the proportion of patients who agree to participate from the total approached, for each arm of the embedded trial. We will assume that patient eligibility for host trial participation will have been assessed before an approach has been made.

Data on recruitment to the host trial will be recorded automatically within the host trial dataset.

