### 6.2.3 Quality of Decision Making

We will also measure the quality of decision making by potential host trial participants. Children and adolescents will be asked to complete a brief decisional scale, adapted from one used within the REFORM trial (unpublished data; [name], [name], [name], [name], [name]) and drawing conceptually on the SURE (3, 4) and DelibeRATE scales (5). When a parent/carer has been involved in the participation decision, we will also ask them to complete the scale. The scale has been adapted to facilitate completion by young children. We will aim to obtain decision quality scores both from individuals who decide to participate in the host trial and those who decline.

In patients who decide to take part, the children and adolescents and/or parent/carer will be asked to complete the decisional scale once the host trial participation documentation has been completed. In patients who decline participation, they will be asked to complete this measure in the clinic or will have them posted at home or emailed, as appropriate.

The adolescent and parent/family versions of the questionnaire contain the same number of questions, with slight changes in the phrasing of questions. The decisional scale contains 9 Likert questions (with 5 possible answer options) and there are a further 3 questions containing space for free text which give participants the opportunity to give further opinion on their experience. There is also a question detailing who filled in the questionnaire (‘patient’ or ‘parent/carer and patient together’). The younger patient version of the questionnaire is of a similar format. The decisional scale contains 3 Likert questions (each with 5 possible answer options) and the further 3 open ended questions (Please see appendix).

The decisional scales will be scored for both the 3 and 9 question version. Answers to each Likert question will be allocated a value of 0-4. The values for each question will be summed to create an overall score, out of 12 and 36, for the two versions of the scale. Up to three missing responses will be allowed on the 9 question scale. One missing value will be allowed on the 3 question version of the scale. A total score will be calculated by replacing the missing values with the mean score from the completed responses given by the participant. Any scores with more than 3 (adolescent and parent/family version) or more than 1 (younger patient version) will not be scored.

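### The decision-quality model adjusts for host trial entry, which follows allocation and is the primary outcome, so no planned model estimates the total effect of the information format

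*SAP*

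**What the plan says.** Section 7.3.3 fits a linear regression to the decision score, "with TRECA allocation and host trial status (whether the participant went on to enter the trial) included as a covariates". Patient and family questionnaires are modelled separately, and a random effect handles clustering.

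The same section plans two further analyses. One repeats the model on fully completed questionnaires. The other narrows the population: "Both the above analyses (in this section) will be repeated for only the participants who went onto to enter a trial". Section 8.3 then pools the trial-level mean differences. It cites section 7.3.2 for them, which is the retention section; from its subject it must mean 7.3.3.

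Elsewhere the covariate appears as an outcome. Section 6.1 states: "The primary outcome is recruitment to each host trial between the MMI only arm and the PIS only arm". The Trial Objectives section says that this phase will evaluate the MMIs and "test their effects on recruitment and retention rates, and decision-making". Section 4.1 plans on an effect of allocation on entry.

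On timing, section 6.2.3 says that those who take part "will be asked to complete the decisional scale once the host trial participation documentation has been completed". It also aims to "obtain decision quality scores both from individuals who decide to participate in the host trial and those who decline".

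**The concern.** Entry to the host trial is not a baseline characteristic. It happens after the participant has been allocated an information format, and it is the behaviour that the format is meant to change. A model that holds it fixed compares arms among people who made the same decision. That has two consequences when the MMI moves recruitment:

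- Any part of the effect on the score that goes with the decision to join is removed.
- If some unmeasured trait, such as attitude to research, drives both joining and the score, arms that were balanced by randomisation are no longer balanced within entrants or within decliners.

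A link between score and entry is plausible. Entrants complete the scale after their paperwork, and items 8 and 9 of the older-patient form ask about the decision itself.

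Section 7 commits to intention-to-treat. Participants do stay in their allocated arm, but the coefficient reported is no longer the comparison that randomisation protects. The SAP gives no reason for the adjustment and does not say that a conditional or direct effect is wanted.

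**Working it through.** **Planned effect on the covariate.** Section 4.1 says that at 20% baseline "an odds ratio of 1.2 would mean an increase in recruitment rate using the MMI to 23.1" per cent, and at 80% that "an odds ratio of 1.2 corresponds to an increase in recruitment rate to 82.8" per cent. Both reproduce from p(MMI) = OR × odds / (1 + OR × odds):

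- 20%: 1.2 × 0.25 = 0.30; 0.30/1.30 = 23.08%; difference 0.0308.
- 80%: 1.2 × 4 = 4.8; 4.8/5.8 = 82.76%; difference 0.0276.
- 50% (inside the SAP's range): 1.2/2.2 = 54.55%; difference 0.0455.

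**Size of the shift.** In least squares, adding entry to a model with allocation changes the MMI coefficient by

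adjusted − total = −b × (p(MMI) − p(PIS)),

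where b is the adjusted score difference between entrants and decliners, and the entry proportions are those among people analysed. Full questionnaire return is assumed here. The SAP gives no value for b. The assumed range is 2.25 to 6.75 points, which is one third of an SD to one SD, using the SD of 6.75 in section 4.2 (BAMP sub-study).

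| Baseline entry | OR | b = 2.25 | b = 4.5 | b = 6.75 |
|---|---|---|---|---|
| 20% | 1.2 | −0.07 | −0.14 | −0.21 |
| 50% | 1.2 | −0.10 | −0.20 | −0.31 |
| 80% | 1.2 | −0.06 | −0.12 | −0.19 |
| 20% | 2.0 | −0.30 | −0.60 | −0.90 |
| 50% | 2.0 | −0.38 | −0.75 | −1.13 |
| 80% | 2.0 | −0.20 | −0.40 | −0.60 |

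At OR 1.0 every entry is zero. The OR of 2.0 is not in the SAP; it shows how the shift grows. Against the 4.5 points that section 4.2 calls meaningful, the shift at OR 1.2 is 0.06/4.5 = 1% to 0.31/4.5 = 7%.

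**Check by simulation.** Settings: 2,000,000 people, no MMI effect on the score, SD 6.75, and a latent trait correlated 0.5 with the score that also drives entry (log-odds 1 or 2 per SD). Baseline entry was 20% or 80%.

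| OR | Allocation only | Adjusted for entry | Entrants only |
|---|---|---|---|
| 1.0 | −0.01 to 0.01 | −0.01 to 0.01 | −0.01 to 0.04 |
| 1.2 | −0.01 to 0.00 | −0.08 to −0.13 | −0.08 to −0.17 |
| 2.0 | −0.01 to 0.00 | −0.27 to −0.58 | −0.26 to −0.75 |

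The formula and the simulation agree. At 20% baseline, OR 1.2 and log-odds 1, the fitted b is 2.91; 2.91 × 0.0308 = 0.09, which takes the allocation-only −0.011 to the adjusted −0.101.

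**A harsher scenario.** Here 65% are recruited under PIS, entering itself adds 4 points, and a shared attitude factor adds 2.5 points per SD and also drives entry. Entrants then score 5.8 points higher overall. With no direct MMI effect, the total and adjusted estimates are +0.13 and −0.08 at OR 1.2, and +0.31 and −0.13 at OR 1.5.

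**Is the total effect available elsewhere in the plan?** No model supplies it. The completed-questionnaire repeat uses the same covariates, and the entrants-only repeat conditions on entry by restriction.

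**The case against.** Five points can be made for the plan.

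- **The harm is conditional.** A reader might infer that the decision-quality result is biased as a matter of fact. The documents do not support that. Whether the MMI changes recruitment is the trial's own question, and the SAP gives no figure linking score to entry. If either link is absent, the shift is zero. This stands.
- **The size is small.** A reader might also take from the harsher scenario that the adjustment will reverse the sign of a real benefit. That depends on an assumed 4-point effect of entering and on a total effect that is itself a fraction of a point. At the planned OR the shift is below the likely precision of single trials. With the Table 1 sizes, SD 6.75, full return and no clustering, the 95% half-width is 1.96 × 6.75 × √(2/n per arm): 1.6 for CHAMP-UK (413/3), 3.2 for BALANCE (100/3) and 0.8 for FORCE (1071/2). This stands.
- **A conditional target could be intended.** Most items rate the information, so comparing arms at a given participation decision is a conceivable aim. The SAP does not state it, and that estimate would still be open to confounding by anything driving both entry and score.
- **Unadjusted scores by arm will be shown.** Section 7.3.3 does summarise scores by allocation, but descriptively, without an estimated difference or interval.
- **Dropping the covariate is not a complete cure.** Decliners answer in clinic, by post or by email, so they may return fewer forms. In the harsher scenario at OR 1.5, with assumed return of 80% of entrants and 20% of decliners, the allocation-only estimate falls to about +0.05 against a total effect of +0.31. It stays closer than the adjusted estimate. This stands and shapes the fix.

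**Conclusion.** The concern holds in conditional form. Section 7.3.3 adjusts for a post-allocation variable that is the primary outcome. If the MMI changes recruitment and score is related to entry, the reported mean difference is not the total randomised effect, no planned model estimates that effect, and section 8.3 pools the affected estimates. At OR 1.2 the shift is about 0.06 to 0.3 points on the 0-36 scale, assuming an entrant-decliner difference of 2.25 to 6.75 points and full return. It grows with the recruitment effect. If the MMI raises entry and entrants score higher, its benefit on decision quality is understated; other sign patterns change the direction. This is a modest flaw in a secondary outcome, worth correcting because the correction is cheap. It does not touch the recruitment result.

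**What to change.** In section 7.3.3, make the main decision-quality model TRECA allocation only, with the cluster random effect in FORCE, and say that it targets the total effect of the information format. Carry that estimate into the section 8.3 meta-analyses. Keep the entry-adjusted and entrants-only models as labelled supplementary analyses that condition on a post-allocation outcome.

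Report questionnaire return by arm and participation decision. Add a sensitivity analysis that weights respondents by the inverse of the return fraction in each arm-by-decision cell; it assumes that respondents represent their cell. Limit it to questionnaire versions whose denominators are available. The recruitment counts alone may not supply them: forms are age-specific, the parent form applies only where a parent was involved in the decision, and section 7.1 says that baseline data exist only for those randomised.

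The cost is a change of SAP wording, slightly wider intervals from dropping a predictive covariate, and a little more analysis work.

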**UKALL**: The UKALL trial is a multicentre, phase III, randomised controlled trial, with two phases of randomisations. The aims are to define whether further refinement of minimal residual disease (MRD) based risk stratification and treatment regimen improves survival whilst reducing overall burden of therapy in children and young adults suffering from acute lymphoblastic leukaemia or lymphoblastic lymphoma.

Table 1 is given below outlining the main characteristics of all the host trials. Table 2 gives the details of the hypothetical study in BAMP. The type of questionnaire are as follows:

- Y = younger patient version
- O = older patient version
- P/F = patient family version

Table 1 – Host trial summary

| Trial | Target Sample Size | Expected TRECA sample size | Type of randomisation in trial | Type of randomisation in TRECA | TRECA arms being used | Decision making questionnaires used |
| --- | --- | --- | --- | --- | --- | --- |
| BALANCE | 66 | 100 | Individual | Individual | PIS, MMI or both | Y, P/F |
| BAMP | 60 | 10 | Individual | Individual | PIS, MMI or both | O, P/F |
| CHAMP-UK | 289 | 413 | Individual | Individual | PIS, MMI or both | Y, P/F |
| FORCE | 696 | 1071 | Individual | Cluster | PIS or MMI | P/F |
| THERMIC-3 | 94 | 118 | Individual | Individual | PIS, MMI or both | Y, O, P/F |
| UKALL | 40 | 50 | Individual | Individual | PIS, MMI or both | Y, O, P/F |

Table 2 – Characteristics of hypothetical BAMP sub-study

| Trial | Target Sample Size | Expected TRECA sample size | Type of randomisation in TRECA | TRECA arms being used | Decision making questionnaires used |
| --- | --- | --- | --- | --- | --- |
| BAMP sub-study | 148 | 148 | Individual | PIS or MMI | O |

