## 4.2 BAMP hypothetical sub-study

We will seek to recruit 148 participants to this sub-study (74 in PIS group and 74 in MMI group). This is to allow for 20% of those randomised not being able to complete the questionnaires (e.g. due to time available or not completing all questionnaires). The questionnaires have 9 Likert scale questions with each of these questions having a score option of 0-4, so the total possible score range is 0-36 (for example 0 means very hard and 4 means very easy; Please see appendix). A difference between groups (MMI versus PIS) of 4.5 (reflecting a mean of 0.5 point different on each of the 9 questions with a Likert scale) would be meaningful. Standard deviation (SD) on the scale of pooled scores is 6.75 (estimated that 95% scores would fall between 4.5 and 31.5 is 27, dividing 27 by 4 for approximate SD = 6.75). Power is 90% and significance level = 0.01. Further information about the questionnaires is given in Section 6.2.3.

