# Randomisation

Allocation to groups will be achieved by random number generator or another randomisation method that suits the practicalities of the host trial. Participants will be randomised 1:1 to either PIS or MMI (two arms) in the BAMP sub-study. In FORCE clusters (hospitals) are randomised to either PIS or MMI. Otherwise, participants will be randomised 1:1:1 to one of PIS, MMI or both.

Masking of the allocation at outcome measurement is not possible but also irrelevant: the patient cannot be masked to the information format s/he will receive but, as s/he will be unaware of the embedded information trial, a lack of masking will not affect his/her responses on the self-completion measures, or have any biasing effect on their decisions on trial participation or continuation.

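### Combined patient decision scores (THERMIC-3, UKALL) are centred by questionnaire version but version is left out of the model, which slightly attenuates the MMI estimate; a version covariate is a cheap improvement

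*SAP*

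**What the plan says.** Section 7.3.3 analyses patient scores by linear regression, "with TRECA allocation and host trial status (whether the participant went on to enter the trial) included as a covariates". When a host trial uses both patient versions, the scores are first "standardised within the trial by subtracting the sample mean score from the observed score and dividing the result by the sample standard deviation". The sample in question "refers to the subset of participants that have used that questionnaire"; no restriction to a TRECA arm is stated, so the arms are pooled by implication. "Then the standard scores for all participants will be analysed as described above", which means the same model, with no questionnaire-version term.

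Table 1 in section 2.2 shows which host trials this reaches. Only two list both Y and O: "THERMIC-3 | 94 | 118 | Individual | Individual | PIS, MMI or both | Y, O, P/F" and "UKALL | 40 | 50 | Individual | Individual | PIS, MMI or both | Y, O, P/F". Both randomise individuals in TRECA, and the Randomisation section gives the ratio: "Otherwise, participants will be randomised 1:1:1 to one of PIS, MMI or both". Section 8.3 then pools the mean differences across host trials.

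**The concern.** Subtracting a version mean is a partial adjustment for version. A full adjustment takes version out of both the outcome and the allocation variable, and a version term in the regression does exactly that. Centring alone treats only the outcome. If MMI recipients are over-represented among users of one version, that version's mean already carries more of the MMI effect, and subtracting it removes some of that effect from the comparison. The loss depends on the squared association between arm and version. Imbalance in either direction therefore shrinks the estimate, and the loss does not cancel over repeated trials.

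At stake is the size of the reported standardised mean difference in two host trials, and their contribution to the patient-score meta-analyses. Section 7.3.3 presents this outcome as a mean difference with a 95% confidence interval, so some accuracy in the estimate matters even where tests are unaffected.

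**Working it through.** The SAP gives no figure of its own for this analysis, so there is nothing to reproduce first.

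**Inputs from the SAP**
- Expected TRECA sample: 118 (THERMIC-3) and 50 (UKALL), three arms, 1:1:1.
- Illustrative effect: borrowed from section 4.2, "A difference between groups (MMI versus PIS) of 4.5", with SD 6.75, so d = 4.5/6.75 = 0.667. That section concerns the BAMP sub-study and the 9-item scale.

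**Assumptions**
- The same d applies on both versions.
- Return rates and the younger-version share are not given. Responder numbers of 118, 50, 30 and 15 are used; 15 is 30% of 50.
- Return of forms does not depend on arm differently for the two versions.
- Host trial status is left out of the simulated models.

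**Step 1. What centring does.** One version mean is subtracted from every arm, so the MMI–PIS difference within a version is kept in full. Attenuation needs a different version mix between arms:

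estimate ≈ true effect × (1 − r²), where r is the correlation between allocation and version.

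Example: two equal arms with 60% and 40% younger, 50% overall. Then r = (0.60 − 0.40) × √(0.25/0.25) = 0.20, r² = 0.04, a loss of 4%.

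**Step 2. Expected loss under randomisation.** With the arm and version totals fixed and arms assigned at random among N responders, the average r² is 1/(N − 1), whatever the version share or the effect size:
- N = 118: 1/117 = 0.9%
- N = 50: 1/49 = 2.0%
- N = 30: 1/29 = 3.4%
- N = 15: 1/14 = 7.1%

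**Step 3. Simulation of the SAP rule** (4,000 trials per setting, d = 0.667, half that effect in the combined arm, 50% younger). The last column is the plan's estimate divided by the estimate with a version term.

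| Responders | Plan: estimate (SE) | With version term: estimate (SE) | Ratio |
| --- | --- | --- | --- |
| 118 | 0.634 (0.216) | 0.640 (0.218) | 0.991 |
| 50 | 0.622 (0.328) | 0.635 (0.335) | 0.980 |
| 30 | 0.611 (0.424) | 0.632 (0.439) | 0.967 |

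The ratios agree with step 2. At 15 responders the plan's rule gave 0.57–0.59 and the version term recovered about 0.04, which is consistent with 7%.

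**Step 4. Inference.** The standard error rises in step with the estimate. Power, plan against plan plus version: 83.4% and 83.2% (118), 46.8% and 46.6% (50), 28.9% and 28.8% (30). With no true effect, the mean estimate is about zero and the rejection rate about 5% under both models.

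**Step 5. The divisor, kept separate.** Even with the version term, the estimates stay below 0.667 because the all-arm SD includes the between-arm spread. In within-arm SD units, all-arm SD = √(1 + between-arm variance of the means):
- Combined arm at half the effect (means 0, 0.667, 0.333): variance = (0.444 + 0.111)/3 − 0.333² = 0.074, SD = 1.036, and 0.667/1.036 = 0.643.
- Combined arm at the full effect (means 0, 0.667, 0.667): variance = 0.889/3 − 0.444² = 0.099, SD = 1.048, and 0.667/1.048 = 0.636.

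This is 3.5–5% in SD units and rescales the estimate and its standard error together.

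**The case against.** The strongest case against raising this is that it has no inferential consequence. Both trials randomise individuals, so imbalance arises by chance only. Power and type I error are the same with or without the version term. The gain in the estimate, 0.006 at 118 responders and about 0.04 at 15, is far below its standard error. The outcome is secondary, the parent/family scores and the recruitment outcome are untouched, and section 7.3.3 also summarises scores by questionnaire type and allocation, so version-specific results stay visible. All of this stands, and it is why the point is minor. It does not make the omission preferable: the result is reported as an estimate with an interval, and the loss runs in one direction only.

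A reader might infer something stronger: that the standardisation strips out a meaningful part of the MMI effect, since simulated estimates fall as low as 0.57 for a true 0.667. The SAP does not support that reading. Much of the gap comes from dividing by an all-arm SD estimated in a small sample. The SAP nowhere defines the target in within-arm SD units, and section 4.2 describes its own 6.75 as an SD of pooled scores. The all-arm divisor is therefore mainly a choice of unit. The extreme case, in which all younger responders in the comparison sit in one arm, is possible but not typical under 1:1:1 randomisation.

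**Conclusion.** The point holds as a small one. In THERMIC-3 and UKALL, centring on the all-arm version mean without a version term attenuates the MMI coefficient when there is a true effect: about 1% at 118 responders, 2% at 50 and up to about 7% at 15. There is no bias under the null and no material change in power or type I error.

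The percentages for the centring part do not depend on d or on the version share. They do depend on the number of forms returned, which the SAP does not give, and on return not differing by arm and version jointly; differential return could produce more imbalance than chance. The absolute figures rest on d = 0.667 from the BAMP sub-study. This is a cheap improvement of low severity, not the correction of a serious bias.

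**What to change.** In section 7.3.3, add questionnaire version (younger/older) as a covariate in the model for the combined patient scores, next to TRECA allocation and host trial status. Add one sentence saying that the resulting mean difference is in units of the all-arm SD of each version within the host trial.

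The cost is SAP wording, one degree of freedom and a slightly larger standard error (0.216 to 0.218 at 118 responders, 0.328 to 0.335 at 50). No new data are needed.

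A within-arm SD for each version, or a separate Hedges g for each version, should not be required. In simulated UKALL trials with 15 forms, 75% of them younger, the per-version within-arm SD was undefined in about 24% and the separate g was not estimable in about 42%. The plan's own all-arm SD was undefined in about 7%.

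### The sensitivity analysis of missing-item replacement requires nine answered questions, so no three-item younger-patient form can enter it and the replacement on that form is never tested

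*SAP*

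**What the plan says.** SAP Section 6.2.3 describes two scored versions of the questionnaire. For the adolescent and parent/family versions, "The decisional scale contains 9 Likert questions (with 5 possible answer options"). For the younger-patient version, "The decisional scale contains 3 Likert questions (each with 5 possible answer options) and the further 3 open ended questions".

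The same section sets one replacement method for both versions: a missing item takes the mean of the items that the participant did answer. Up to three items may be missing on the longer version. For the shorter version, "One missing value will be allowed on the 3 question version of the scale".

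Section 7.3.3 then adds a sensitivity analysis. Its purpose is given as "To assess the robustness of the method used to replace the missing values", with no limit to one version. Its rule is to repeat the analysis "using only the questionnaires in which all 9 questions were answered".

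Table 1 in Section 2.2 lists the forms used in each host trial (Y younger patient, O older patient, P/F parent/family). The largest trial with a patient form reads "CHAMP-UK | 289 | 413 | Individual | Individual | PIS, MMI or both | Y, P/F", so its only patient form is the younger one.

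**The concern.** A sensitivity analysis of missing-item handling should change one thing only, namely what is done with incomplete forms. This rule also removes every complete younger-patient form, because three items cannot supply nine answers.

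There are two consequences. First, replacement on the three-item form, which Section 6.2.3 permits, is not examined by any analysis in the SAP. Secondly, where a trial uses both patient forms, the main analysis combines standardised younger and older scores, while the sensitivity analysis would contain older patients alone. A difference between the two could then come from the age group, from the imputation, or from both. Agreement would say nothing about the younger form.

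**Working it through.** The SAP states no figure on this point to reproduce. The check compares the item counts with the inclusion rule and then counts the people concerned.

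**Item counts (Section 6.2.3 and the example forms in Appendix 12.2)**

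- Longer version: 9 scored items, each 0 to 4, maximum 9 × 4 = 36. A form with all 9 answered can exist.
- Younger version: 3 scored items, each 0 to 4, maximum 3 × 4 = 12. Even if the 3 open questions and the opening question on whether any information was seen are counted, 3 + 3 + 1 = 7, which is below 9. No younger form can meet the rule on any way of counting.
- Both maxima match the totals of 12 and 36 in Section 6.2.3.

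**Effect by trial (forms and expected TRECA sample sizes from Table 1)**

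| Trial | Expected | Patient form | Patient-form sensitivity analysis as written |
| --- | --- | --- | --- |
| BALANCE | 100 | Y | empty |
| CHAMP-UK | 413 | Y | empty |
| THERMIC-3 | 118 | Y and O | older patients only |
| UKALL | 50 | Y and O | older patients only |
| BAMP | 10 | O | works |
| FORCE | 1071 | none | not applicable |

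**Size**

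- Trials with a patient form: 100 + 413 + 118 + 50 + 10 = 691.
- Younger form only: 100 + 413 = 513, and 513/691 = 74.2%.
- Left at most: 10 + 118 + 50 = 178, and 178/691 = 25.8%. This needs every THERMIC-3 and UKALL patient to use the older form.
- The split between younger and older patients in THERMIC-3 and UKALL (118 + 50 = 168) is not given. The excluded share therefore runs from 74.2% (none younger) to (513 + 168)/691 = 681/691 = 98.6% (all younger). At an assumed even split it is (513 + 84)/691 = 86.4%.
- With none of the 168 on the younger form, younger forms remain the majority unless form return in BALANCE and CHAMP-UK falls below 178/513 = 35% of the return elsewhere.
- Against all six host trials: 691 + 1071 = 1762, and 513/1762 = 29.1%.

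The hypothetical BAMP sub-study (148, older form) is left out of these counts because Section 7 analyses it separately.

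**Parent/family forms.** All six host trials use this nine-item form, and Section 7.3.3 analyses it separately from the patient forms. The rule works there as written.

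**The case against.** The strongest reply is that this is a drafting slip. The stated purpose covers the replacement method in general, and that method applies to both versions, so fully completed forms were probably meant. That is a fair inference, but the SAP does not say so, and Section 6.2.3 is careful to keep the two versions apart. If instead the analysis was meant for nine-item forms only, the three-item replacement is left untested. Either way the sentence needs correcting.

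Four stronger readings are tempting, and the documents do not support them.

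- *A change in the mix of trials would drive the result.* Section 7 analyses each trial separately, so in BALANCE and CHAMP-UK there would be no result to mislead anyone. The mix could change only under pooling, and Section 8.3 does not clearly pool this analysis. It promises four meta-analyses and refers to Section 7.3.2, which is the retention section. Patient and parent/family forms, each for all respondents and for entrants only, already make 2 × 2 = 4. Main and sensitivity analyses, each for all respondents and for entrants only, also make 2 × 2 = 4. The text does not settle which is meant.
- *A difference would reflect age and not imputation.* In THERMIC-3 and UKALL it would mix the two, so imputation is not excluded as a cause.
- *Most TRECA data would be lost.* The 74% concerns the patient-form analysis only.
- *The short form is more exposed because one item is a third of its score.* The longer version allows three of nine, also a third, so the largest imputed share is the same. What differs is that a replaced item rests on two answers on the short form and on at least six on the long one.

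It also limits the harm that Section 7.3.3 reports missing responses for each question by type of questionnaire. Readers will see how much replacement the younger forms needed, though not whether it mattered.

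**Conclusion.** Wrong as written, but minor: it concerns a sensitivity analysis of a secondary outcome. The rule cannot be met by any younger-patient form, and this follows from the item counts alone. It leaves the patient-form sensitivity analysis empty in two trials and restricted to older patients in two more.

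The figure of 74% (513 of 691) counts people approached, which is what the expected TRECA sample sizes in Table 1 represent, and not forms returned. It assumes equal form return across trials. The SAP gives no response rates and does not say how many younger children will complete a form, so it should be read as an indication of scale. The main decision-quality estimates and the primary recruitment result do not change.

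**What to change.** In Section 7.3.3, define completeness by version: restrict the sensitivity analysis to forms with every scored item answered, meaning nine of nine on the older-patient and parent/family forms and three of three on the younger-patient form. In Section 8.3, state whether this sensitivity analysis is among those pooled, and apply the same definition there only if it is. The cost is one sentence in 7.3.3 and, if needed, a clause in 8.3, entered in the SAP amendment log. No new data are required.
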